Develop materials	• Development of MOOC with clinical content and focus on quality improvement in clinical settings • MOOC developed in consultation with people with dementia and carers, industry experts, educational designer • Development of implementation plan pro forma for clinicians • Establish group norms and standards of collaboration • Support for implementation clinicians to develop further site-specific resources
Educate	• Provision of training through seven-module MOOC • Phone orientation meeting with research team and face-to-face start up meeting to begin implementation plan brainstorming • Implementation plan reviewed by a person with dementia and their carer, quality improvement expert, and clinical expert • Support for implementation clinicians to gather feedback from ‘practice teams’ within their organisation • Regular audit and feedback based on clinician self-report and client dyad-report
Educate through peers	• Implementation plan reviewed by QIC peer • Ongoing communications within the QIC via online forums and monthly videoconferencing
Inform and influence stakeholders	• Use mass media, professional organisation newsletters, and industry publications to share information about the project and highlight implementation clinician plans
Restructure	• Implementation clinicians take a lead in quality improvement in their organisations • Site-specific implementation plan may involve restructuring or changes in structure, equipment, or records
Quality management	• Iterative quality improvement process using PDSA cycles • Ongoing peer supervision with subgroup of QIC members • Support for implementation clinicians to gather ongoing feedback from ‘practice teams’ within their organisation • Fidelity checking based on content of clinical interactions (via clinician self-report and patient and client dyad-report) • Monthly QIC meetings in which each clinician will report their plan activity for the month • Revisiting of implementation plan after each monthly meeting with update log; revised plan submitted 6 months after implementation • Reminders • Provision of client tools to increase uptake of best practice (to half of the sites) • Ongoing access to people with dementia and carers and clinical, quality improvement experts throughout implementation and follow-up
Finance	

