#### Educate

Education for implementation clinicians will be delivered after a 9-month pre-intervention period and include written resources, webinars, expert feedback, collaboration and peer supervision, and online learning. The main component of the education will be an intensive, eight-module ‘massive open online course’ (MOOC) to upskill implementation clinicians on the clinical evidence base related to occupational therapy for people with dementia, physical activity for people with dementia, or carer support. The MOOC will focus on quality improvement techniques in clinical settings. Implementation clinicians will be guided through the development of an associated implementation plan unique to their service context and informed by service gaps and barriers and facilitators to improvement identified during the planning phase. The MOOC will be co-designed with people with dementia and carers to ensure it reflects their needs and experiences. Input will also be sought from clinical, aged care industry, quality improvement, and educational design experts to ensure it is rigorous, up-to-date, and effectively facilitates learning. Implementation clinicians will have access to people with dementia, carers, and clinical and quality improvement experts to review their plan and provide feedback. A peer review process will also allow implementation clinicians to give and receive feedback from another member of their QIC.

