#### Quality management

Once reviewed, clinicians will implement their plan and participate in monthly virtual meetings with their QIC to benchmark and brainstorm strategies to overcome any noted roadblocks. They will iteratively review and update their plans using PDSA cycles [47] with support from people with dementia and carers and clinical and quality improvement experts. Clinician reports of the consultation will be audited, cross-referenced with client dyad reports, and anonymously fed back to facilitate self-assessment.

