### Outcomes

The outcomes and measures that will be used for this study are presented in Table 3. Outcomes of interest relate to guideline adherence, implementation of the QIC methodology, service level effectiveness and harms, and client dyad outcomes.

**Table 3 Tab3:** Project outcomes

Outcome domain	Details of measurement
Guideline adherence	
Exercise guideline adherence	Full adherence when: a) Clinician checklist explicitly references a discussion about current physical activity levels, and; b) Specific needs and barriers to physical activity are identified, and; c) Treatments/strategies recommended are clinical indicated based on needs/barriers, and; d) A written treatment plan for physical activity or exercise is provided to the person with dementia
Occupational therapy guideline adherence	Full adherence when: a) Home environment assessment has occurred (where applicable), and; b) Clinician checklist explicitly references identification of primary concern/s of person with dementia and carer, and; c) A written treatment plan to address needs of person with dementia and carer or give specific advice about suitable activities (that are tailored, of interest, and match capabilities) is provided
Carer support guideline adherence	Full adherence when: a) Clinician checklist explicitly references that the needs of the carer have been discussed during the consultation, and; b) Clinician checklist explicitly references clinically indicated provision of information about programs providing respite for the carer and/or other carer support services, and; c) A written treatment plan detailing key carer concerns and strategies to manage these is provided
Implementation	
Uptake	• Exposure: the extent to which clinicians use the materials and online training course • Initial use: initial changes in adherence to guideline recommendations
Sustainability	• Continued changes in adherence to guideline recommendation.
Feasibility	• Recruitment: attraction of implementation clinicians and participating organisations • Consent rate for people with dementia and their carers agreeing to be contacted for follow-up • Maintenance: involvement in the program and contribution to data collection • Withdrawals

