#### Guideline adherence

The primary outcome of the implementation evaluation is changes in guideline adherence over time. Guideline adherence will be assessed using monthly checklists completed by implementation clinicians about their consultations with people with dementia and/or carers. Clinicians will complete the checklists for the first ten consecutive consultations each month. Clinicians will be asked to provide a ‘snapshot’ of the consultation including its purpose, content, and outcomes. A process for guideline adherence scoring was modelled on methods used in Kortekaas et al. [48] and van Fenema et al. [49]. Key indicators of guideline adherence were developed in consultation with clinical and consumer experts (see Table 3). Two independent researchers will rate whether the practice reported by the clinician was inadequately (− 1), partially (or unclear; 0), or fully adherent (+ 1) to the relevant recommendation. In cases of disagreement, a third external clinical academic will be contracted to make a final decision. A follow-up phone interview with a random selection of client dyads each month up to 5 weeks after the consultation will be used to verify these reports, and ‘agreement’ between the client dyad and clinician will be assessed. Phone interviews will be conducted by the study team with both the person with dementia and their carer where possible, or just the carer where they are directly participating as a client of clinicians in the ‘carer support’ or the person with dementia is unable to participate in a phone call. People with dementia who attend the consultation alone (including those who live in long-term care) will not be contacted by phone. Interviews will gather perspectives from the dyad or carer about their recollection of the consultation and the extent of guideline adherence from their perspective. Clinician and client dyad data will be triangulated with field notes from QIC meetings, online message board participation, and other contact with the research team.

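### Unclear checklists are scored the same as partial adherence, so the primary outcome cannot tell clearer documentation from changed care

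*Protocol article*

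**What the plan says.** Under Guideline adherence, the protocol article sets the scoring rule for the primary outcome. Two researchers separately score the consultation as the clinician describes it: −1 for inadequate adherence and +1 for full adherence. For the score between these the wording is "partially (or unclear; 0". The raters therefore judge the clinician's report, not the consultation itself, and a report they cannot interpret receives the middle score.

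Table 3 (Outcomes) ties full adherence partly to what is written on the form. For exercise the first condition is "Clinician checklist explicitly references a discussion about current physical activity levels". For carer support it is "Clinician checklist explicitly references that the needs of the carer have been discussed during the consultation". The occupational therapy criteria contain a condition of the same kind.

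On timing, the Educate section says: "Education for implementation clinicians will be delivered after a 9-month pre-intervention period". Table 2 lists among the education strategies "Regular audit and feedback based on clinician self-report and client dyad-report", and the Quality management section says: "Clinician reports of the consultation will be audited, cross-referenced with client dyad reports, and anonymously fed back to facilitate self-assessment".

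The Quantitative analysis section fits a segmented regression to 18 monthly points, 9 before and 9 after, and looks for level and trend changes. It describes each point only as the extent of adherence that month. The Discussion states that there is no control group and that some reporting bias may remain.

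**The concern.** Once both states are recorded as 0, the data no longer show which forms were partial and which could not be rated. That would matter little if the share of unclear forms were stable. Here there is reason to expect change: clinicians are trained on the topic, then have their own reports audited and fed back, all after the pre-period. If they then write fuller reports, some forms leave the unclear group and are scored on their content, although the consultations may be no different.

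With no control group, such a change in documentation falls in the same comparison as the intervention effect. The Discussion argues that a covariate confounds only if it predicts the outcome and changes with the timing of the intervention, and expects none of that kind. Clarity of the checklist could meet both conditions. What is at stake is the reading of the primary result: a level or trend change could be partly a change in form-filling, and the recorded scores would not show how much.

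**Working it through.** The plan gives no figure for the unclear share, so there is none to reproduce. The stated 83% power plays no part here; the only benchmark used is the planned 15% change.

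**Inputs from the protocol article.** Scores are −1, 0 and +1, with unclear at 0 (Guideline adherence). There are up to 300 checklists a month for 18 months (Quantitative analysis), so up to 300 × 18 = 5,400. Phone interviews cover up to 180 dyads (Participants).

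**Assumptions.** Care is held constant. Let *d* be the fall in the unclear share. Among the forms that become clear, let *f* be the share describing full adherence and *i* the share describing inadequate adherence; the rest are partial. The protocol gives none of these.

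**Formulas.** A form that becomes clear moves from 0 to +1 if care was full, stays at 0 if partial, and moves from 0 to −1 if inadequate. Hence:

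- change in percent fully adherent = *d* × *f*, which is never negative;
- change in mean score = *d* × (*f* − *i*), which may take either sign.

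**Unclear share falling from 30% to 10%, so *d* = 0.20:**

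| *f* | *i* | Mean score: 0.20 × (*f* − *i*) | Percent full: 20 × *f* |
|---|---|---|---|
| 0.75 | 0.05 | +0.14 | +15.0 points |
| 0.50 | 0.20 | +0.06 | +10.0 points |
| 0.33 | 0.33 | 0.00 | +6.6 points |
| 0.20 | 0.50 | −0.06 | +4.0 points |
| 0.00 | 0.75 | −0.15 | 0.0 points |

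In the limiting case *f* = 1 the figures would be +0.20 and +20 points. With these mixes and that limiting case, and falls of 15 to 30 percentage points, the range is −0.225 to +0.30 in mean score and 0 to +30 points in percent full.

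**What it takes to reach 15.** A 15-point rise in percent full with no change in care needs *d* = 0.15 / *f*: 15% of all forms becoming clear if *f* = 1, 20% if *f* = 0.75, 30% if *f* = 0.50. If 15% is instead read as a share of the two-point score range (0.15 × 2 = 0.30), it needs *d* × (*f* − *i*) = 0.30, for example 30% of all forms becoming clear and every one of them fully adherent.

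**Coverage of the phone check.** 180 / 5,400 = 3.3% of checklists.

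**The case against.** The strongest reply has five parts.

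- **Direction and size.** A reader might infer that the rule must inflate the effect, perhaps by the whole 15%. The documents do not support this. On the three-level score, a clearer form can also reveal inadequate care and lower the mean. The Objectives say adherence to these recommendations is known to be poor, and full adherence requires three or four conditions together, including a written plan. A small *f* is therefore quite plausible, and then the effect on the mean score could be nil or negative. This stands.
- **Timing.** A reader might place the shift exactly at the break. Training takes 8 weeks, with plan review and monthly meetings afterwards, and nothing says that training or feedback teaches form completion. Practice with the form itself (up to 90 forms per clinician by month 9) falls in the pre-period trend. This stands: a gradual shift would show more in the trend than in the level.
- **Recoverability.** A reader might conclude that the two states can never be separated. Clinicians return the checklists to the study team, so they could be re-rated, at the cost of going through up to 5,400 forms.
- **Safeguards.** There are two raters and an adjudicator, phone verification, triangulation with field notes, and an admitted reporting bias. None of these splits the code. An agreed unclear form still scores 0, and the phone check covers about 3.3% of forms, leaves out people who attend alone, and has no stated rule for changing a score.
- **Where it belongs.** Sensitivity analyses are often left to an analysis plan. The shared code, however, is fixed in this article, and a later plan cannot split it without re-rating.

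**Conclusion.** The point holds, within limits. The scoring rule merges missing information with observed partial adherence, and the design gives a plausible reason for the unclear share to change after the pre-period. The primary outcome could therefore move with care unchanged.

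The direction depends on the monthly summary, which the article leaves open. It is upward or zero for percent fully adherent, and of unknown sign for the mean score. The size is not known. The illustration of 0 to +15 points, or −0.15 to +0.14, rests on an assumed fall in unclear forms from 30% to 10% and on the assumed mixes shown. The documents do not show that unclear forms are common, that their share will fall, or that a false positive result is likely. The case for change is that the safeguard is nearly free if adopted before rating and laborious afterwards.

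**What to change.** Have the raters record unclear or not rateable as its own code, distinct from partial. Keep the planned scoring, with unclear counted as 0, as the primary analysis. Leaving unclear forms out of the primary denominator would assume that vagueness is unrelated to the quality of care, so exclusion is better kept as a sensitivity analysis.

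Report the unclear share by month, before and after training. Then repeat the segmented regression:

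- for the mean score, with unclear set to +1 and then to −1;
- for percent fully adherent, with unclear counted as full (counting it as not full is the planned coding already);
- for either summary, with unclear forms excluded.

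Using one value throughout brackets the result only if the unclear forms conceal a similar mix before and after training; the report should say so.

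The cost is one extra rating code and a few sensitivity runs. The separate code does not deal with a form that says nothing on a Table 3 item and is therefore rated partial or inadequate, rather than unclear. That part of the reporting bias remains a limitation to state.

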#### Process evaluation

Feasibility and acceptability among service providers of the QIC model for improving service provision for people with dementia and carers will be assessed by tracking the level of interest from potential implementation clinicians and following up with those who originally expressed interest but declined participation after receiving further information to identify key barriers. We will also track the consent rate of client dyads agreeing to be contacted by phone following the consultation to determine acceptability of this method of data collection. In-depth interviews with implementation clinicians and their managers early in the project will establish expectations, perceived acceptability of the QIC, potential barriers to participation, current practice, organisational cultures, and previous experiences with innovation. Interviews will be repeated at the end of the 18 months to understand their experience of the QIC and the education package and factors that influenced their uptake. The interview questions were developed based on the Consolidated Framework for Implementation Research qualitative interview guide, developed to capture the many constructs known to be important to implementation success [50].

Interview data will be supplemented with the 23-item NoMAD survey instrument based on Normalisation Process Theory, completed by implementation clinicians to assess their perception of the integration of their quality improvement plan [51]. Practical knowledge of the implementation clinicians in quality improvement will be measured using vignettes and the Quality Improvement Knowledge Application Tool Revised [52]. Detailed field notes related to project acceptability, feasibility, and sustainability will be kept and analysed including email, online messaging, phone, and face-to-face contact between the implementation clinicians and research team.

Costs associated with establishing and running the QIC will be estimated. Total costs include costs of providing the intervention (personnel, technology, stipends, and development and distribution of educational materials) and in-kind contribution required for each site estimated using a ‘bottom-up’ micro-costing approach. Costs will be estimated using administrative data and resource use questionnaires administered to key implementation site personnel. The monetary benefits of adopting and implementing the QIC, from implementation clinicians’ point of view, will be determined using contingent valuation techniques [53]. This technique allows for a monetary value to be placed on a good or service that is not yet available in the marketplace. The maximum amount of money that implementation clinicians would be willing to pay for the perceived benefits (buying price) of implementing the QIC will be estimated using their responses to a willingness to pay (WTP) questionnaire. As per best practice guidelines [53, 54], the WTP questionnaire will (a) identify the benefits that are likely to be realised from the QIC, (b) assess prior knowledge about QIC and attitudes toward it, and (c) establish respondents’ WTP.

Finally, implementation clinicians and managers will complete an organisational network map of their implementation site to describe the structure of their services, relationships between staff members, and potential sources and supporters of innovation. These maps can be used to examine the complex interactions between structures and people that might not be captured in an interview [55]. Maps will also be used to examine the penetration of the project in terms of the variety of sites, funding models, professional backgrounds, level of seniority, and types of roles engaged with the QICs. Clinician checklists, interviews, client dyad phone calls, and field notes will be examined to assess whether participation improved the reach of services to previously underserviced clients.

#### Involvement of people with dementia and carers

We will assess the impact of involvement of people with dementia and carers in the study design, conduct, and reporting on the quality of the intervention (from the perspective of clinicians) during the process evaluation. The impact of involvement in research of people directly affected by the conditions being researched on research quality and outcomes is underreported [56], and knowledge of impact is important to establishing best practice and policy directives [45, 56]. Modelled on Dudley et al. [46], qualitative interview questions will be included to assess implementation clinicians’ perspectives on the value of the contributions of people with dementia and carers, impact on clinicians’ learning and quality improvement activities, and any negative impacts. Results will be reported per recommendations by Staniszewska et al. [57].

#### Service and client-level outcomes

During the client dyad phone interview up to 5 weeks after the consultation, both the person with dementia (where applicable) and their carer will be asked to rate their satisfaction with the consultation using an amended version of the Patient Satisfaction Questionnaire Short-Form (PSQ-18) [58]. Seven PSQ-18 items were selected because they were relevant to the types of consultations delivered by QIC clinicians. They assess satisfaction with the time spent with the health professional and their communication and interpersonal manner on a 5-point Likert scale (total score range 7–35). Items on the PSQ-18 have adequate internal consistency (all >  0.65) [58].

Adverse events that may reflect the safety of the QIC model will be reported by implementation clinicians during monthly QIC meetings and in in-depth interviews. Client dyads will also be asked to reflect on the recommendations made during the consultation by the implementation clinician and report any negative consequences.

We will also assess the impact of the QIC model and guideline adherence on quality of life for the person with dementia (clients of clinicians in the exercise and occupational therapy QICs) or burden for the carer (clients of clinicians in the ‘carer support’ QIC) during this phone interview. These outcomes will be assessed a second time with a follow-up phone interview up to 7 weeks after the first, to identify sustained impact.

Quality of life will be assessed using the DEMQOL-Proxy [59], a 31-item questionnaire administered with the carer. The DEMQOL-Proxy asks the carer to report the extent to which the person with dementia has exhibited a variety of emotions and functional behaviours in the past week on a 4-point Likert scale, as well as a global quality of life item. Scores are summed to a total of 31–124, with higher scores indicating better QOL. The DEMQOL-Proxy has demonstrated good discriminant validity and converges well with the non-dementia-specific EQ-5D-5L [60]. The shortened 12-item version of the Zarit Burden Interview will be used to establish and monitor carer burden for client dyads of clinicians in the ‘carer support’ QIC. This shortened version correlates well with the original 21- and 22-item versions [61] and has high internal consistency (*α* = 0.87) and discriminant validity (AUC = 0.99) [62]. Carers are asked to report the frequency of their feelings of stress and burden associated with caring for the person with dementia on a 5-point Likert scale, summed to a maximum score of 48.

